## LIST OF ABBREVIATIONS

| Abbreviation    | Full name                                                                                                                                             |
|-----------------|-------------------------------------------------------------------------------------------------------------------------------------------------------|
| ADHD     | Attention-deficit Hyperactivity Disorder                                                                                                              |
| BDNF     | Brain-Derived Neurotrophic Factor                                                                                                                     |
| CPR      | (Danish) Civil Registration System                                                                                                                    |
| CVD      | Cardiovascular Disease                                                                                                                                |
| DTU FOOD | National Food Institute, Technical University of Denmark                                                                                              |
| EFSA     | European Food Safety Authority                                                                                                                        |
| FiSK     | [Forsknings- og formidlingsprojekt om Fisk, børn, Sundhed og Kognition]
Research and communication project on fish, children, health and cognition |
| GCP      | Good Clinical Practice                                                                                                                                |
| GWAS     | Genome Wide Association Study                                                                                                                         |
| HbA1c    | Glycosylated haemoglobin                                                                                                                              |
| ID       | Identification                                                                                                                                        |
| NEXS     | Department of Nutrition, Exercise and Sports                                                                                                          |
| PCB      | Polychlorinated Biphenyls                                                                                                                             |
| SD       | Standard deviation                                                                                                                                    |
| SNP      | Single Nucleotide Polymorphism                                                                                                                        |
| TEQ      | Toxic Equivalents                                                                                                                                     |
| TWI      | Tolerable Weekly Intake                                                                                                                               |
| 25(OH)D  | 25-hydroxy Vitamin D                                                                                                                                  |

# **1. BACKGROUND**

## **1.1 Organization and partners**

FiSK Junior, which is described in this protocol, is a research project within the overall research and communication project FiSK [Forsknings- og formidlingsprojekt om Fisk, børn, Sundhed og Kognition] (Research and communication project on fish, children, health and cognition). The overall FiSK project is a partnership collaboration between Department of Nutrition, Exercise and Sports (NEXS), University of Copenhagen and four Danish aquariums: Kattegatcentret in Grenaa, Den Blå Planet in Copenhagen, Fiskeri- og Søfartsmuseet in Esbjerg, and Nordsøen Oceanarium in Hirtshals. The overall aim of the FiSK project is to investigate the potential effects of fatty fish on children's health, cognitive function and behavior as well as communicating our existing evidence-based knowledge on fish intake and human health to Danish families, and to provide playful, fun and inspiring experiences with fish as food. The communication part of project FiSK will be located at the four aquariums, and the research part (FiSK Junior), which is described in this protocol, will be conducted at NEXS.

## **1.2 Scientific background**

### **1.2.1 Fish – a nutrient-rich food that we consume too little of**

The Danish Veterinary and Food Administration recommends that Danes consume 350 g/week fish, hereof 200 g/week fatty fish such as salmon, mackerel and herring (1). Danish 4-9-year-old children have a median intake of about 70 g/week fish and less than 10% of the children reach the recommended weekly intake (2).

Fish is an important dietary source of iodine, selenium, zinc, and high quality proteins, and especially oily fish are rich in n-3 long-chain polyunsaturated fatty acids (n-3 LCPUFA). Oily fish is also an important source of vitamin D, especially during winter when the contribution of vitamin D from sun exposure is negligible in Denmark, and the risk of vitamin D insufficiency is high in both children and adults (3). Intake of n-3 LCPUFA may protect from cardiovascular disease (CVD) in adults (4) and may affect cognitive function and development (5). The potential effects of oily fish on cardiometabolic health and cognitive function have, to our knowledge, not been investigated in children.

### 1.2.2 n-3 fatty acids and cardiometabolic health

Meta-analyses generally indicate that consumption of fish and n-3 LCPUFA reduce cardiovascular mortality in adults (4,6–8). From randomized controlled trials in adults it is well known that intake of n-3 LCPUFA (typically in the form of fish oil) reduces cardiometabolic risk factors especially blood pressure (9), heart rate (10) and the concentration of triglycerides in plasma (11). Our previous randomized trials with fish oil to infants, toddlers and adolescents indicate that n-3 LCPUFA have comparable effects in children (12–15), but only few studies have investigated this in children.

### 1.2.3 Oily fish and cardiometabolic health

Randomized controlled trials administering oily fish rather than fish oils have mainly been performed in adults, not in children. These trials show mixed results, but most indicate that consumption of oily fish can improve cardiometabolic risk markers, especially blood pressure and plasma triacylglycerols (16–22). In the OPUS School Meal Study, where more than 700 school children received school meals rich in fish *versus* habitual lunch packs in a randomized design, we previously found that the school meals reduced plasma triacylglycerol, insulin, and blood pressure despite evoking a small increase in waist circumference (23). Further analyses indicated that a main part of the beneficial effects was explained by the increased fish intake (24). However, to our knowledge no randomized trials have investigated the effect of fish consumption *per se* on cardiometabolic health in children.

### 1.2.4 Cardiometabolic markers in childhood

Although very few children get CVD, elevated cardiometabolic risk markers and metabolic syndrome are seen in childhood (25), and the Bogalusa Heart Study (26) and the Cardiovascular Risk in Young Finns Study (27) demonstrated that blood lipid profile and blood pressure show tracking from childhood and adolescence to adulthood. Therefore, small but persistent reductions in cardiometabolic markers in childhood may be important for long term cardiometabolic risk. As healthy dietary habits, that may evoke such changes, are partly founded in childhood it seems reasonable to promote health and prevent life style diseases through healthy dietary habits from childhood.

### 1.2.5 n-3 fatty acids and cognitive function

During brain development n-3 LCPUFA are incorporated into the brain, particularly during the first years of life. The rate by which this process occurs has been shown to be affected by diet and is believed to play a role in the cognitive development of the child (28). Most trials investigating the effects of n-3 LCPUFA on cognitive function have been conducted in formula-fed infants or infants of mothers receiving fish oil. Meta-analyses of these randomized trials do not confirm an overall pronounced beneficial effect of n-3 LCPUFA on neurodevelopmental outcomes during the first two years of life (29–31). However, this may be because the effect of n-3 LCPUFA is gender-dependent (32,33). Most studies in young children have used broad developmental scales and have not

examined effects on specific cognitive function, but data indicate that n-3 LCPUFA may specifically affect outcomes related to attention as opposed to memory and processing speed (34,35). Only few studies have examined the effects of n-3 LCPUFA and cognitive outcomes in school children (36–40). However, the studies have mainly been performed in low-income populations, which are quite different from the Danish population, and have mainly used pure n-3 LCPUFA and not fish. Also, the results of these studies have not been analyzed gender-specifically.

### **1.2.6 n-3 fatty acids and behavioral and emotional outcomes**

Dietary n-3 LCPUFA deficiency has been shown to increase motor activity (41) and to affect emotional outcomes such as anxiety and depression, in rodents (41,42). Both pre- and postnatal dietary regimes rich in n-3 LCPUFA have been seen to reduce stress vulnerability and responses to corticosterone (42,43). The described DHA-affected brain functions can be linked to monoaminergic neurotransmitter pathways – *e.g.* anxiety, attention and physical activity, which has been shown to be affected by changes in n-3 LCPUFA intake (41). A few randomized trials in healthy pre-pubertal school children have showed that children supplemented with fish oil had a more relaxed mood or reduced impulsivity and anti-social behavior compared to control (40,44). Also, lower scores related to traits of attention-deficit hyperactivity disorder (ADHD) have been observed after fish oil supplementation in children living in a low-income area (45). In adults, cross-national data on fish intake indicate that intake of fish and n-3 LCPUFA status play a role in symptoms of depression and patients with depression have been shown to have low n-3 LCPUFA concentrations in their blood and brain (46,47). Therefore, higher habitual dietary n-3 LC-PUFA intake may be protective against mood swings and may prevent mood dysregulation (48). However, as it is not possible to draw any firm conclusions based on the existing studies and further research within this area is needed, especially in children.

## **2. OBJECTIVE**

The main objective of FiSK Junior is to investigate whether intake of fatty fish compared to poultry affects cardiometabolic markers in 8-9 year-old Danish school children. Moreover, we will investigate the potential effects on cognitive function, behavior and emotions.

The study has two primary outcomes: Diastolic blood pressure and plasma triacylglycerol concentration.

## **3. METHODS**

### **3.1 Study design**

The study has a block-randomized controlled 12-week parallel design (**Figure 1**). It will include two groups of 100 children each; one group that receives fatty fish and one group that receives poultry.

The study participants will be 8-9 year-old healthy Danish children who will be enrolled from summer 2016 to April 2017. Apart from an information meeting the study consists of a pre-visit, a baseline visit and an endpoint visit which will be held at Department of Nutrition, Exercise and Sports (NEXS), [name].

[figure not shown]

**Figure 1. Flow diagram of the study activities**

### 3.2 Study foods

Participants in the intervention group will receive oily fish (with minimum 2 g of fat per 100 g) primarily as fillets of salmon, but also other types of fatty fish such as mackerel in tomato sauce and marinated herring, whereas participants in the poultry group will receive primarily chicken and chicken products (e.g. liver pate, chicken sausage) but possibly also small amounts of duck and turkey. As far as possible, the products provided to the two groups will be matched for energy and fat content. The parents will be instructed that the study fish and poultry should substitute some of the fish and meat usually consumed by the child. Apart from this, the parents will be instructed to maintain the child's usual dietary and physical activity habits during the intervention. The participants will be asked to consume 300 g/week of fish or poultry, operationalized as two times per week as dinner meal and as bread topping / for lunch three times per week, based on typical portion sizes as estimated by the National Food Institute, Technical University of Denmark (49). The goal of 300 g per week is within the national recommendation (1) and will provide

approximately 1 g/day n-3 LCPUFA, which has been shown to reduce blood pressure and plasma triacylglycerol in previous fish oil trials (11,14,15).

Study fish and poultry will be provided as fresh, frozen, and canned foods from NEXS free of charge together with a recipe booklet containing easy recipes and suggestions for preparation of the allocated study foods. The recipe booklet produced for the poultry group will contain poultry recipes resembling those fish recipes provided to the fish group, but with extra oils and fats added when needed to match the fat and energy content of the recipes in the two groups. As most children in this age group eat dinner with their family (50) fish and poultry for dinner will be provided for the whole family/household, whereas lunch products and bread toppings, which are typically eaten in school and more individually, will be provided for the participating child only. The participating child's family will be encouraged to eat the provided study foods for dinner together with the child to enhance compliance. Poultry is chosen as the control food as it is considered to be healthier than the alternative, red meat (51), and has a similar amount of protein and a relatively low content of n-3 LCPUFA compared to oily fish.

### **3.3 Randomization and blinding**

Randomization will be performed in blocks of 12 children, to assure equal allocation to the two study groups over the year. A computer generated randomization list with 200 consecutive 'order numbers' (1, 2, 3, ..., 200) will be produced before study start by a staff member not involved in the practical study work. When meeting for the pre-visit each participant will be assigned a unique ID number (in the format D218xxx). At the end of the baseline visit the prospective participant is assigned to one of the two intervention groups by the investigator querying the randomization sequence, thus linking participant ID to a number in the randomization sequence and consequently randomly to one of the intervention groups. For example, if the child with ID number D218004 is the second child to finish his baseline visit, he will be assigned to 'order number' 2 on the randomization list, which, according to the list corresponds to e.g. poultry group. This procedure assures optimal data handling and quality, as all test and papers related to the child can be assigned the unique study ID number already from the pre-visit, while at the same time assuring that group allocation is not performed until after the baseline measurements. This procedure ensures blinding of both participants and investigators until the baseline measurements have been completed. Due to the taste and nature of the intervention foods, blinding of study staff and participants is not possible through the entire study.

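### One disclosed block size of 12, queried by the investigator with no stated concealment of later entries, does not secure blinding of investigators until baseline is complete

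*Protocol*

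**What the plan says.** Section 3.1 plans two equal groups, with the pre-visit, baseline and endpoint visits all at one department. Section 3.3 sets the method: "Randomization will be performed in blocks of 12 children, to assure equal allocation to the two study groups over the year". A list of 200 order numbers "will be produced before study start by a staff member not involved in the practical study work". Children take order numbers in the sequence in which they finish the baseline visit, and the assignment is obtained "by the investigator querying the randomization sequence, thus linking participant ID to a number in the randomization sequence".

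The same section describes the arrangement as "while at the same time assuring that group allocation is not performed until after the baseline measurements" and concludes: "This procedure ensures blinding of both participants and investigators until the baseline measurements have been completed". It then accepts that staff and participants cannot stay blind for the rest of the trial.

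It does not say that the block size is withheld from study staff, that entries beyond the current one are hidden when the sequence is queried, or that the person who made the list also holds and releases it.

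**The concern.** Carrying out allocation after baseline controls when an assignment becomes official. It does not stop anyone foreseeing it. With one site, one list, one printed block size and arms that are visible once food is handed out (Table 1 has the first batch given at the baseline visit), a running tally is easy to keep. Near the end of a block the remaining assignments can be worked out. If the query shows the list itself, no tally is needed.

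Staff have some discretion before allocation:

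- Blood pressure sets may be repeated up to four times in a visit (section 4.2.1), so their number is not fixed.
- Skinfolds are taken by hand (4.1.2) and cognitive tests are staff-instructed (4.3).
- Staff may judge that a child does not want to take part or continue (3.5.3, 3.8).

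Foreknowledge could therefore influence who reaches allocation, in what order, or how baseline is measured. Baseline outcome values are the covariate in the analysis of covariance (5.2). Selection of this kind cannot be repaired in the analysis.

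**Working it through.** The protocol gives no figure for predictability, so there is none to reproduce.

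**Inputs.** Block size 12 and a list of 200 order numbers (section 3.3). Equal allocation, hence 6 + 6 per block (section 3.1).

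**Assumptions.** Permuted blocks; staff know the block size and all earlier assignments; the list itself is not seen.

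**Assignments certain in advance.** For a block of 2k, the expected number fully determined by earlier ones is 2k/(k + 1). With k = 6 this is 12/7 = 1.714, or 1.714/12 = 14.3%. The list holds 16 full blocks plus 8 entries. Full blocks give 16 × 1.714 = 27.43. The last 8 entries add about 0.02, for a total of about 27.4 of 200.

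**Assignments predictable with at least 75% probability.** An exact recursion over the block gives 2.58 of 12, or 21.5%. This includes the 1.71 that are certain.

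**Correct guesses when always naming the arm that is behind.** The expected number per block is k + (2^(2k)/C(2k,k) − 1)/2. With k = 6 this is 6 + (4096/924 − 1)/2 = 6 + 1.716 = 7.716, and 7.716/12 = 64.3%. Over the 200-entry list it is 128.1/200 = 64.0%, against 50% by chance.

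**Comparison of block sizes** (full blocks, same assumptions):

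| Block size | Certain in advance | Guessed correctly |
|---|---|---|
| 4 | 33.3% | 70.8% |
| 6 | 25.0% | 68.3% |
| 8 | 20.0% | 66.6% |
| 12 | 14.3% | 64.3% |

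**Mixed sizes** (simulation of 5,000 lists of 200, naming the arm that is behind): sizes 4, 6 and 8 give 68.0% correct; sizes 8 to 16 in steps of 2 give 64.0%.

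Naming the arm that is behind requires no knowledge of the block size, so varying sizes around 12 leaves the guess rate where it is. What it mainly removes is certainty about where a block ends. Concealed single release removes the possibility of reading ahead, which is not in the figures above.

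**The case against.** A reader might infer that section 3.3 contradicts itself. It does not. Allocation follows the baseline measurements, and no passage says that anyone learns the arm earlier. The gap is one of concealment: *ensures* promises more than the described steps deliver.

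A reader might also infer that allocations are generally predictable. About 86% are not determined, the best guess gains 14 percentage points over chance, and both figures need a complete tally. Twelve is a fairly large block, less guessable than 4, 6 or 8, and there is a reason for blocking: baseline visits run from August to April (section 3.4).

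The room for bias is limited too. The list is generated independently. Written consent precedes all study activity (3.7, 9.2). Blood pressure is read by an automated device after rest (4.2.1), and the other primary outcome, plasma triacylglycerol, is a laboratory value. Skinfolds and cognitive tests are not primary outcomes. That staff would steer the order of finishing is an inference; no passage describes it.

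Finally, a reader might note that 200 is not a multiple of 12, so exactly 100 per group is not guaranteed. The cut-off last block can only shift the split to between 98 and 102, which is immaterial beside the expected drop-out of up to 15–20% (3.6).

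All of this stands and keeps the point modest. It does not supply the missing safeguard: the protocol still does not hide later entries or the block size from the person who queries the sequence.

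**Conclusion.** The concern holds as a concealment gap. With permuted 1:1 blocks of 12, and staff who know the block size and past assignments, about 14% of assignments (about 27 of 200) could be known with certainty before the baseline visit ends, and about 64% could be guessed correctly. If querying the sequence shows the list, more could be known; the text neither says so nor excludes it. The claim that investigators stay blind until baseline is complete is therefore not secured by the procedure as written. The documents do not show that anyone is unblinded early or that bias would follow, and the effect on the primary outcomes cannot be sized from them. A cheap change to the stated procedure is worth making because the problem cannot be corrected afterwards.

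**What to change.** Before the first child is allocated:

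- Regenerate the list with randomly varying block sizes around 12, for example 8 to 16, and do not disclose the sizes to study staff or print them in documents they use.
- State in section 3.3 that each assignment is released singly from a concealed list, and only after the baseline visit is logged as complete. The release can be made by the uninvolved person who made the list, by a concealed electronic module, or from sequential sealed envelopes.
- Do not move to smaller blocks such as 4, 6 and 8.

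The cost is a new list, a few changed sentences and a small continuing task: up to 200 single releases between August 2016 and April 2017. Section 3.3 currently has the list-maker produce the list only, so this task must be assigned. Calendar balance becomes slightly looser: the largest possible within-block imbalance rises from 6 (half of 12) to 8 (half of 16). The tally-based guess rate stays near 64%; the gain is in removing certainty at block ends and any chance of reading ahead.

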### **3.4 Time plan**

Participants will be enrolled from summer 2016 to April 2017. The baseline visits will be conducted during August 2016 - April 2017. Endpoint visits will be conducted during November 2016 - June 2017. The duration of the intervention period will be  $12 \pm 3$  weeks.

### **3.5 Study participants**

#### **3.5.1 Inclusion criteria**

Children must:

- Be 8 - 9 years of age at the start of the intervention
- Be healthy
- Like oily fish and chicken
- Be willing to be randomized to eat fish or chicken
- Not consume fatty fish more than once per week 3 months prior to intervention start
- Not consume fish oil 3 months prior to intervention start
- Speak Danish in order to understand the study procedures

Moreover:

- Parents must read and speak Danish, in order to be properly informed about the study procedures
- The child must live in a household with  $\leq 5$  persons

